## Abstract

**Introduction:** The worldwide spread of the novel coronavirus (SARS-CoV2) has prompted numerous countries to restrict public life. Related measures, such as limits on social gatherings, business closures, or lockdowns, are expected to considerably reduce the individual opportunities to move outside the home. As physical activity (PA) and sport participation significantly contribute to health, this study has two objectives. The objectives of this study are to assess changes in PA and well-being since the coronavirus outbreak in affected countries. Additionally, we will evaluate the impact of digital home-based exercise programs on PA as well as physical and mental health outcomes.

**Method:** A multinational network trial will be conducted with three planned phases (A, B, and C). Part A consists of administering a structured survey. It investigates changes in PA levels and health during the coronavirus outbreak and measures the preferences of the participants regarding online training programs. Part B is a two-armed randomized-controlled trial. Participants assigned to the intervention group (IG) will complete a digital 4-week home exercise training (live streaming via internet) guided by the survey results on content and time of program. The control group (CG) will not receive the program. Part C is 4-week access of both CG and IG to a digital archive of pre-recorded workouts from Part B. Similar to Part A, questionnaires will be used in both Part B and C to estimate the effects of exercise on measures of mental and physical health.

**Results and Discussion:** The ASAP project will provide valuable insights into the importance of PA during a global pandemic. Our initial survey is the first to determine how governmental confinement measures impact bodily and mental well-being. Based on the results, the intervention studies will be unique to address health problems potentially arising from losses in PA. If proven effective, the newly developed telehealth programs could become a significant and easy-to-distribute factor in combating PA decreases. Results of the study may hence guide policy makers on methods to maintain PA and health when being forced to restrict public life.

**Study Register:** DRKS00021273.

## Introduction

Abundant evidence supports the value of physical activity (PA) and exercise as essential cornerstones of physical and mental health (1–3). For instance, it has been shown that regular movement lowers all-cause mortality by up to 80% while decreasing the odds of developing cardiovascular, neurological, musculoskeletal or psychiatric diseases (4). In view of these effects, specific guidelines detailing optimal PA have been developed for a variety of populations including children or older adults (5, 6) and health professionals and policy makers strive to implement them with considerable effort (7–10).

Since the outbreak of the novel coronavirus (SARS-CoV-2) in December 2019 and the classification as a global pandemic in March 2020, the opportunities to engage in sport and exercise have been greatly limited (11). Due to governmental regulations that restrict activities in public life [e.g., bans of public gatherings, business closures or city lockdowns; (12)], the ability to move freely has been reduced for the general population. Similar to initial actions in China, various countries (among others, United States of America, France, Germany, Spain, United Kingdom, and Italy) have taken measures that limit activities. The restrictions in access to sports clubs, gyms, and self-organized outdoor activities are assumed to result in a considerable decrease in global and individual PA levels (11).

Reductions in PA are not only relevant because of the unexploited benefits of regular movement. Inactivity and sedentary behavior, characterized as time spent in sitting, lying or reclined posture at low energy expenditures, have substantial adverse effects on health (13). A meta-analysis, pooling data from more than 1.3 million participants, demonstrated that particularly sitting and TV viewing time are both strongly associated with premature death (13). Such activities and other sedentary behavior may increase in populations affected by the coronavirus pandemic.

Government measures that aimed to control illness after the virus outbreak in China limited movement for millions of people over weeks to months (12). As other countries with registered cases implemented restrictive measures too, it is of the utmost importance to understand how such restrictions will change PA, physical health and mental well-being. Further, novel strategies may be required to maintain or improve PA at home. The objectives of our study are to examine the effects of public restrictions by geography on (a) PA and (b) individual well-being using an international population-based survey. Using these results, we plan to investigate the feasibility of digital home-exercise programs as well as their effectiveness in increasing physical and mental health.

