**Figure 1 F1:**
[figure not shown]
Visualization of the project flow in each center. In study part A, participants are recruited for a cross-sectional survey (ASAP questionnaire). Upon completion they are made aware about the opportunity of registering for the randomized, controlled trial (RCT, study part B). Participants are also recruited among individuals who have not completed the survey. After completing the RCT, participants will receive access to a video database for another 4 weeks (study part C).

All participants will provide informed consent. Outcomes in all three portions of the study (Part A, B, and C) are assessed using digital questionnaires. After being provided with information on the investigation including purpose, aims, voluntary nature of participation and data use on the first page of the questionnaires, each individual will be asked to choose whether to select the “Participate” button, which signalizes digital consent to participate in the study. All data will be either collected anonymously without patient identifiers (survey for study Part A) or retrospectively anonymized (Parts B and C).

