### Participants

The target population will include residents aged 18 and older from countries with (1) officially registered cases of the novel coronavirus (SARS-CoV-2) and (2) active governmental restrictions limiting public life via bans of public gatherings, forced restrictions of social, contact business closures, or lockouts. Recruitment will be performed by means of advertising in social media platforms (e.g., Youtube, Facebook, Twitter, Instagram) as well as health-related institutions (e.g., national chapters of the Exercise is Medicine initiative).

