#### Study Part B

Based on the results of study part A, the second part will consist of a multicenter, two-armed, randomized-controlled parallel group trial. Participants in the intervention group (IG), for a period of 4 weeks, will receive online workouts with video live-streaming using the appropriate software (e.g., Zoom, Zoom video communications, San Jose, California, USA; BlackBoard, Washington, DC, USA). Duration, frequency, and contents will be selected balancing (a) the needs of the population as indicated via the ASAP questionnaire and (b) scientific recommendations for exercise prescription. For example, the minimum training frequency will be once per week and minimum duration will be 10 min (21). To allow a higher degree of standardization between the countries, the instructors will be provided with modifiable demo workouts exhibiting different content-related focuses (e.g., strength, endurance, postural control/balance, cognition, relaxation), which can be individually adapted. The control group (CG) will not receive an intervention and is instructed to complete the outcome assessments (see below). Randomization (1:1 ratio) will be performed using a software algorithm of the online database used for survey delivery (Soscisurvey, Soscisurvey GmbH, Munich, Germany). To allow concealed group allocation, the participants will be automatically informed by the system about allocation upon survey completion at baseline.

A two-fold approach is used for recruitment. Firstly, upon completion of the ASAP questionnaire (study part A), each participant will be informed about the opportunity to participate in the subsequent intervention trials (Study Parts B and C). Second, the same recruitment strategies used for the initial survey (social media advertising and promotion via associations and societies) will be used to enhance recruitment.

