### Data Processing and Statistics

All datasets will be analyzed using intention-to-treat. The findings from the ASAP questionnaire (Study Part A) will be descriptively reported and presented using appropriate measures such as mean ± standard deviation or median and interquartile range depending on distributions and scales of measurement. Additionally, the significance of variable associations (e.g., between physical activity levels and markers of well-being) will be examined using correlation and regression analyses.

To estimate the risk of non-response bias, wave analyses will be conducted according to Lewis et al. (26). Specifically, the responses of the first 10% percent of the participants (early responders) will be compared to those of the last 10% (late responders) by means of inferential statistics. The rationale behind this is that early responders are assumed to be more motivated than late responders which can be compared to non-responders. Hence, if the wave analyses do not provide significant findings, absence of non-response bias is concluded.

For study Parts B and C (randomized, controlled trial/controlled crossover trial), a prospective meta-experiment approach will be applied (27). For each country, the mean pre-post-differences between-groups including 95% confidence intervals (95% CI) will be calculated at the different time points. An a priori sample size calculation using an algorithm specifically designed to account for between-site variance in multi-center trials was performed (28). When achieving a sample size of *n* = 544 with an included drop-out rate of 20%, the trial will have 80.3% power to detect pre-post-differences with a minimal effect size (Cohen's *d*) of 0.25 at an alpha level of 0.05. To account for potential between-center variance, the data collected in each country will be pooled using a random-effects model (29). This leads to an aggregated effect size (weighted mean differences) demonstrating the overall effectiveness of the intervention while the different countries can still be compared by means of inspecting the 95% CI's. Heterogeneity between countries will be quantified by means of the *I*^2^ index (30). To further explore its potential sources (e.g., country, age, sex, baseline physical activity), a meta-regression with continuous and factorial independent variables will be performed (31).

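### Part A is labelled population-based, but entry is by open self-selection, so its conclusions, including country comparisons, can be claimed for respondents only

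*Protocol article*

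**What the plan says.** The last paragraph of the Introduction gives the Part A objective: to examine the effects of public restrictions by geography "on (a) PA and (b) individual well-being using an international population-based survey". The Participants section defines who is meant: "The target population will include residents aged 18 and older from countries with (1) officially registered cases of the novel coronavirus", with active governmental restrictions as the second condition.

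The same section gives the route in: "Recruitment will be performed by means of advertising in social media platforms", together with "health-related institutions (e.g., national chapters of the Exercise is Medicine initiative". Study Part B confirms that the survey used these routes when it refers to "the same recruitment strategies used for the initial survey (social media advertising and promotion via associations and societies". The text after Figure 1 adds that, once the purpose and aims have been shown, "each individual will be asked to choose whether to select the “Participate” button".

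For the analysis, Data Processing and Statistics states: "The findings from the ASAP questionnaire (Study Part A) will be descriptively reported and presented using appropriate measures such as mean ± standard deviation", with correlation and regression in addition. It also plans a wave analysis of the first 10% against the last 10% of participants, and takes a non-significant result to show that non-response bias is absent.

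**The concern.** Calling a survey population-based tells the reader that its figures can be carried over to a defined population. Here that population is the adult residents of each restricted country. Recruitment by advertisement and voluntary opt-in does not provide this, because nobody is drawn from the population and the chance of entering is unknown.

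People who like exercise may be more likely to respond. One named channel is an exercise-promotion initiative, the questionnaire asks about exercise-programme preferences, and its completion leads to an invitation to an exercise trial. If such people also changed their activity differently from others, the Part A summaries would differ from the population values.

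Two uses are exposed. The Abstract presents the survey as determining how confinement measures affect well-being. Study Part B treats the questionnaire answers as the needs of the population when choosing workout content. The comparison by geography has the same limit: each country's figure describes whoever responded there.

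**Working it through.** **1. Label against entry route.**

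- Stated property: population-based (Introduction).
- Stated target: adult residents of countries with registered cases and active restrictions (Participants).
- Stated entry: advertising and institutional promotion (Participants; Study Part B), then a voluntary click (text after Figure 1).

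The third item describes an open convenience sample. A fuller document could add analysis detail, but it could not turn advertising into a draw from a population.

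**2. Whether the wave analysis closes the gap.** Early and late responders all came through the same channels and all opted in. If both groups are self-selected to the same degree, the comparison rejects only at its nominal 5% level, however large the selection. People whom the adverts never reached, or who did not click, appear in neither group.

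The test may also be weak for differences it could see. The article gives no Part A sample size, so the totals below are assumed, with a two-sided 0.05 level (sidedness is not stated) and a proportion near 50%.

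| Responders | Groups | Power, 10-point difference | Power, 5-point difference |
|---|---|---|---|
| 500 | 50 v 50 | 17% | 7% |
| 1,000 | 100 v 100 | 29% | 11% |
| 5,000 | 500 v 500 | 89% | 35% |

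**3. Size.** The document has no Part A figure to reproduce; n = 544 belongs to Part B. For illustration, let s be the share of exercise-interested people in the population, q their share in the sample, and pe and pn the proportions with a PA decrease among them and among others. Then

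survey − true = [q·pe + (1 − q)·pn] − [s·pe + (1 − s)·pn] = (q − s)(pe − pn).

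All inputs are assumptions: s = 30–50%, q = 70–90%, pe = 50–60%, pn = 30%.

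- Smallest: (0.70 − 0.50)(0.50 − 0.30) = 0.04, or 4 points.
- Largest: (0.90 − 0.30)(0.60 − 0.30) = 0.18, or 18 points (survey 57%, true 39%).
- No excess (q = s): 0.
- Roles reversed, if keen exercisers switch to home training (pe = 30%, pn = 60%): (0.90 − 0.30)(0.30 − 0.60) = −0.18, or −18 points.

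Sample size does not enter the formula, so more responders do not reduce the bias.

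**4. Dependence on the summary.** Assume PA changes of −40% in exercisers and −10% in others, and a 40% population share of exercisers.

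- Averaging percentage changes over people, with a 70% sample share: 0.70(−40) + 0.30(−10) = −31, against 0.40(−40) + 0.60(−10) = −22. The gap is 9 points. With a 50% sample share the gap is 0.10 × 30 = 3 points.
- Percentage change in mean minutes, with exercisers assumed at three times the others' baseline. At 70%: (0.70×3×0.40 + 0.30×0.10)/(0.70×3 + 0.30) = 0.87/2.40 = 36.25%. At 40%: 0.54/1.80 = 30.0%. The gap is 6.25 points. At 50%: 0.65/2.00 = 32.5%, a gap of 2.5 points.

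So even with the sign and the subgroup changes fixed, the answer depends on which summary is reported.

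**The case against.** The phrase occurs once, in the Introduction. The design section calls Part A a structured, multinational cross-sectional survey, recruitment is openly described, the analysis is mainly descriptive, and no national estimate is promised. On this view the point is one loose adjective. Part of that stands: nothing is concealed, and the correction is mostly wording. But the phrase sits in the objective, the target population is stated in matching terms, and the methodological considerations in the Discussion cover over-reporting of PA but not self-selection.

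Several stronger readings are tempting, and the document does not support them.

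- A reader might infer that the figures describe exercise enthusiasts and overstate the PA loss. The channels are general social-media platforms and health-related bodies, with the exercise initiative only as an example. The make-up of the sample and the sign of any bias are both unknown.
- A reader might infer that policy makers will be guided by a biased PA loss. The policy sentence in the Abstract follows the statement on the telehealth programmes and concerns methods to maintain PA.
- A reader might infer that country contrasts reflect different recruitment mixes. The Participants section gives one strategy for all countries, so differing mixes are possible but not documented.
- A reader might fault the plan for having no weighting. A condensed article may leave that to a fuller document, so its absence is not a finding here.

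**Conclusion.** The objective claims a property that the stated recruitment does not provide. This is a conflict between two statements in the article and needs no assumption. Part A can describe its respondents; it cannot, as designed, estimate changes in the adult populations under restriction or compare those populations by geography.

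Over-representation of exercise-interested people is a reasonable possibility and not an established fact. Its effect cannot be sized from the document: the illustrative results run from −18 to +18 percentage points, include zero, and rest wholly on assumed inputs. The wave analysis cannot detect selection shared by early and late responders, so a null result there says nothing on this point.

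A reader might extend the concern to the trial. The Part B comparison is randomised within those who enrol, so it is not biased by this; only its generalisability is touched. The correction should be made because it is cheap and changes what Part A may conclude.

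**What to change.** - In the objective, describe Part A as an open online convenience survey instead of a population-based one.
- Limit Part A conclusions, including comparisons between countries, to respondents. Do not cite a null wave analysis as evidence that the sample represents the target population.
- Report changes in PA and well-being also by pre-outbreak PA level from the NPAQ-short already collected. State that this level is recalled, that the instrument was adapted to include occupational time, and that the same recalled value enters the PA change, so the strata are descriptive.
- Treat post-stratification by age and sex as an optional sensitivity analysis at most. It needs external population margins for every country and does not remove selection on exercise interest within age and sex groups.

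The cost is a narrower claim and a few extra tables. No new data are needed for the first three changes.

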## Materials and Methods

### Ethical Standard and Study Design

The ASAP (**A**ctivity and health during the **SA**rs-CoV2 **P**andemic) project (Figure 1) consists of a structured, multinational cross-sectional survey (study Part A), a two-armed, randomized-controlled, multicenter parallel group trial (study Part B), and a controlled multicenter crossover trial (study Part C). It will be conducted according to the Guidelines of Good Clinical Practice and adhering to the Declaration of Helsinki. This study protocol reports according to the Standard Protocol Items: Recommendations for Interventional Trials (SPIRIT) guidelines (14). Approvals are obtained from the study center's review board (Ethics committee of the faculty of psychology and sport sciences at Goethe-University Frankfurt) as well as from all universities actively included into participant recruitment. The intervention parts of the study have been prospectively registered at the German Registry of Clinical Trials (DRKS00021273).

**Figure 1 F1:**
[figure not shown]
Visualization of the project flow in each center. In study part A, participants are recruited for a cross-sectional survey (ASAP questionnaire). Upon completion they are made aware about the opportunity of registering for the randomized, controlled trial (RCT, study part B). Participants are also recruited among individuals who have not completed the survey. After completing the RCT, participants will receive access to a video database for another 4 weeks (study part C).

All participants will provide informed consent. Outcomes in all three portions of the study (Part A, B, and C) are assessed using digital questionnaires. After being provided with information on the investigation including purpose, aims, voluntary nature of participation and data use on the first page of the questionnaires, each individual will be asked to choose whether to select the “Participate” button, which signalizes digital consent to participate in the study. All data will be either collected anonymously without patient identifiers (survey for study Part A) or retrospectively anonymized (Parts B and C).

### Participants

The target population will include residents aged 18 and older from countries with (1) officially registered cases of the novel coronavirus (SARS-CoV-2) and (2) active governmental restrictions limiting public life via bans of public gatherings, forced restrictions of social, contact business closures, or lockouts. Recruitment will be performed by means of advertising in social media platforms (e.g., Youtube, Facebook, Twitter, Instagram) as well as health-related institutions (e.g., national chapters of the Exercise is Medicine initiative).

### Procedures and Interventions

#### Study Part A

In the first part of the project, a structured multi-national survey will be administered during a 2-week period. The ASAP questionnaire is answered digitally and requires about 5–10 min to complete.

The survey instrument has four sections. The first portion assesses demographic data including age, sex and country of residence. The second section captures self-reported physical activity levels and exercise habits prior to and since the outbreak of the coronavirus. The questions have been newly constructed or adopted from valid measures in order to account for the specificities of the situation. Physical activity levels will be assessed using the Nordic Physical Activity Questionnaire-short (NPAQ-short, 15). The 2-item instrument measures the total time spent in free time during moderate to vigorous physical activities and during vigorous physical activities only. The questions were adapted to also account for working/occupational time. The NPAQ-SF has been shown to be reliable and was validated to monitor compliance with the WHO recommendations on physical activity (15). The third section of the ASAP questionnaire addresses the physical and mental well-being of the participants, again comparing the situation before and after the outbreak. Also, this part consists of questions newly constructed as well as psychometrically validated and cross-culturally adapted questionnaires. Regarding the latter, bodily pain is assessed using the sub-scale of the SF-36 questionnaire and mental well-being is measured using the WHO5-scale (16, 17). In the final section, we examine the preferences of the participants for exercise programs that will be developed based on the answers (e.g., total time, type(s) of exercise and activity).

The ASAP questionnaire was developed using an expert consensus process similar to that described in a previous investigation (18). Briefly, after agreeing on the scope and contents of the questionnaire, an initial version of the instrument was independently reviewed by the consensus team members which included physicians, physiotherapists, movement scientists, and sports scientists. Their blinded feedback was used to refine the questionnaire. For content validation, the questionnaire was sent to experts from different professions not belonging to the research team involved in its development (19). To increase face validity, members of the target population without background from a health profession were asked to provide feedback on comprehensibility and clarity of the questionnaire (20). The assessment tool is available in seven languages [Dutch, English, German, French, Italian, (Brazilian) Portuguese, Spanish]. Clarity and comprehensibility have been validated via forward and back translation by native speakers.

